### Inclusion data

The flow diagram (Figure 3) presents the processing of clusters and students through the initial phases of the PRAMILAP.

**Figure 3 F3:**
[figure not shown]
**Flow diagram of the initial phases of the progress of clusters and individuals in PRALIMAP**.

At cluster enrolment, the mean overall high school size was 812 students (range 283-1,893 students), and 29% had more than 1,000 students. The mean grade 10 size was 265.5 students (72-568). The mean grade 10 participants cluster size was 227.4 students (57-478). Thus, among the 6,371 grade 10 students, 5,458 (85.7%) underwent at least one baseline measurement, without any difference in participation in anthropometric and self-administered measurements. High school participation rates highly differed (from 72.0% to 99.1%) and were higher in general and technological than vocational high schools (86.6% vs 80.9%, p = < 0.0001) and in the rural administrative department of Vosges than in the other 3 departments (89.3% vs 85.1%, p = 0.0014). Finally, participation rates differed significantly but only slightly between strategy and control schools: educational strategy (86.9% vs 84.3%, p = 0.003), screening strategy (84.2% vs 87.1%, p = 0.001) and for environmental strategy (84.6% vs 86.7%, p = 0.013).

As compared with participants, non-participants were significantly older (p = < 0.0001) and more often had unemployed parents (p = 0.0143) and school backwardness (p < 0.0001). Boys and girls participated equally. Adolescents' baseline characteristics, overall and by strategy, are presented in Table 3, 4 and 5 and were similar to the French grade 10 population [29]. Students were in the expected age range, with more than 70% aged 15 years old. In total, 36%, 70%, 53% and 50.1% of students had school backwardness, were in grade 10 in a general and technological school, were girls and the family head was employed, respectively, as compared with 20%, 67%, 54% and 41%, respectively, in the French grade 10 population [29].

**Table 3 T3:** Baseline sociodemographic characteristics of students, overall and by assigned strategy

	**Overall^¶^**	**Educational** **strategy**		**Screening** **strategy**		**Environmental** **strategy**	
				
		**No**	**Yes**	**No**	**Yes**	**No**	**Yes**
	**N = 5,458**	**N = 2,483**	**N = 2,975**	**N = 2,771**	**N = 2,687**	**N = 2,794**	**N = 2,664**
	**%**	**%**	**%**	**%**	**%**	**%**	**%**
							
**Mean age (years)**	15.8*	15.7^¥^	15.7^¥^	15.7^¥^	15.7^¥^	15.7^¥^	15.7^¥^
**Gender (% girls)**	52.9	56.8	53.6	56.5	53.6	54.8	55.4
**General and technological course**	69.7	78.6	83.3	77.9	84.5	78.9	83.5
**School boarding status**							
Non-boarder	22.6	21.9	21.4	21.1	22.1	24.8	18.2
Half-boarder	68.2	70.4	68.4	68.5	70.1	66.1	72.7
Full Boarder	9.2	7.7	10.3	10.4	7.8	9.1	9.1
**Schooling**							
Classic	61.4	64.9	67.2	65.8	66.6	65.2	67.1
Advance placement at school	2.1	2.2	2.8	2.3	2.8	2.6	2.5
Late placement at school	36.4	32.9	29.9	31.9	30.7	32.2	30.4
**Residence (Rural)**	47.0	47.1	50.3	54.3	43.3	46.2	51.6
**Social and professional class of the family head**							
Farmers, shopkeepers, craftsmen, managers	7.3	7.8	8.3	8.6	7.6	7.2	9.0
Executives	12.6	14.4	13.7	11.1	17.0	15.8	12.1
Intermediate jobs	18.5	18.5	21.0	17.7	22.1	20.9	18.8
Employees, workers	50.1	50.4	46.2	52.3	43.9	46.4	49.9
Inactive (unemployed, retired)	11.4	8.9	10.8	10.4	9.5	9.7	10.2
**Parents occupation****							
Neither of the 2 parents works	7.0	5.2	6.5	6.6	5.1	5.0	6.8
One of the 2 parents works	31.3	29.8	30.2	31.0	29.0	28.8	31.2
The 2 parents work	61.7	65.1	63.4	62.4	65.9	66.2	62.0
**Family income level****							
Low	6.9	6.3	6.7	7.5	5.5	6.0	7.0
Average	33.3	33.6	34.4	33.9	34.2	34.4	33.7
High	59.8	60.1	58.9	58.6	60.3	59.6	59.3
**Parental physical activity level****							
Low	54.9	53.1	53.1	54.3	51.8	52.7	53.4
Moderate	3.8	4.4	3.3	4.2	3.4	3.8	3.8
High	41.2	42.5	43.6	41.5	44.7	43.4	42.8
**Parents considered overweight****	39.1	40.0	40.2	40.1	40.2	40.4	39.8

¶ Overall baseline characteristic parameters are estimated according to stratification and cluster design

¥ Standard Deviation = 0.7

* Standard Error of the Mean = 0.02

** Declared by adolescents

**Table 4 T4:** Baseline nutritional attitudes and behaviours of students, overall and by the assigned strategy

	**Overall^¶^**		**Educational** **strategy**				**Screening** **strategy**				**Environmental** **strategy**			
					
			**No**		**Yes**		**No**		**Yes**		**No**		**Yes**	
	**N = 5,458**		**N = 2,483**		**N = 2,975**		**N = 2,771**		**N = 2,687**		**N = 2,794**		**N = 2,664**	
								
	**%/** **mean***	**SEM****	**%/** **mean***	**SD^¥^**	**%/** **mean***	**SD^¥^**	**%/** **mean***	**SD^¥^**	**%/** **mean***	**SD^¥^**	**%/** **mean***	**SD^¥^**	**%/** **mean***	**SD^¥^**
														
**Knowledge score (0-100)**	50.9	0.5	51.9	9.1	51.2	9.0	51.6	9.0	51.4	9.1	51.7	9.1	51.3	9.0
														
**Dietary guidelines followed**														
Fruits and vegetables (≥ 5^#^)	13.0		12.3		14.5		13.0		14.0		13.4		13.6	
Meats, eggs and fishes (1-2^#^)	94.7		94.7		95.1		95.0		94.8		95.2		94.6	
Sugary foods (2-3^#^)	33.3		35.2		33.1		32.6		35.5		33.4		34.7	
Dairy product (3-4^#^)	40.8		40.3		43.3		42.1		41.8		41.6		42.3	
Starchy foods (3 to 6^#^)	69.1		70.7		71.0		71.1		70.7		71.6		70.1	
Drinks (≥ 5^#^)	85.9		85.5		86,0		85.6		85.7		84.9		86.7	
Number of meals per week (21-28)	61.1		62.6		64.1		64.1		62.7		64.0		62.8	
														
**Nibbling**	70.9		70.0		68.2		69.3		68.8		67.5		70.7	
														
**Physical activities guidelines followed**	47.1		45.6		47.3		45.9		47.2		46.3		46.8	
														
**Number of nutritional guidelines followed**	4.3	0.04	4.3	1.3	4.4	1.3	4.3	1.3	4.3	1.3	4.4	1.3	4.3	1.3
≤ 2	9.3		8.1		8.2		7.9		8.5		8.1		8.3	
3	18.3		18.1		17.2		17.4		17.7		16.8		18.4	
4	30.0		30.6		27.9		30.1		28.2		30.1		28.1	
5	25.4		26.0		26.5		26.2		26.3		25.8		26.7	
6	12.7		12.6		15.1		14.1		13.8		14.4		13.5	
≥ 7	4.2		4.6		5.2		4.4		5.5		4.8		5.1	

¶ Overall baseline characteristic parameters are estimated according to stratification and cluster design

* Data are mean when SD is displayed or percentages

** Standard Error of the Mean

¥ Standard Deviation

# Number of daily servings recommended by nutritional guidelines

**Table 5 T5:** Baseline health and anthropometric characteristics of students, overall and by the assigned strategy

			**Educational** **strategy**				**Screening** **strategy**				**Environmental** **strategy**			
					
	**Overall^¶^**		**No**		**Yes**		**No**		**Yes**		**No**		**Yes**	
	**N = 5,458**		**N = 2,483**		**N = 2,975**		**N = 2,771**		**N = 2,687**		**N = 2,794**		**N = 2,664**	
								
	**%/** **mean***	**SEM****	**%/** **mean***	**SD^¥^**	**%/** **mean***	**SD^¥^**	**%/** **mean***	**SD^¥^**	**%/** **mean***	**SD^¥^**	**%/** **mean***	**SD^¥^**	**%/** **mean***	**SD^¥^**
														
**Body mass index (kg/m^2^)**	21.7	0.1	21.5	3.3	21.7	3.6	21.7	3.7	21.5	3.3	21.6	3.6	21.6	3.4
														
**Body size (IOTF classification)**														
Thinness Grade 3	0.2		0.1		0.3		0.3		0.2		0.1		0.4	
Thinness Grade 2	0.8		0.5		0.7		0.6		0.7		0.7		0.6	
Thinness Grade 1	4.5		5.0		3.7		4.5		4.1		4.5		4.2	
Normal	74.9		76.1		76.0		74.7		77.4		75.6		76.5	
Overweight	14.9		14.6		14.9		15.7		13.9		15.0		14.6	
Obese	4.6		3.6		4.3		4.3		3.7		4.2		3.8	
														
**Waist circumference (cm)**	73.1	0.7	73.0	8.5	72.1	9.2	72.7	8.9	72.3	8.8	73.6	9.3	71.4	8.3
														
**High waist circumference (Canada classification)**	13.4		13.2		11.1		12.3		11.7		14.9		9.0	
														
**Eating behaviour disorders (EAT-40)**														
Low risk (< 17.5/100)	81.3		81.2		82.3		81.4		82.2		82.1		81.5	
Moderate risk (17.5/100 - 30/100)	9.9		9.8		10.1		9.9		9.9		9.2		10.7	
High risk (≥ 30/100)	8.8		9.0		7.6		8.7		7.9		8.7		7.8	
														
**Hospital Anxiety and Depression (HAD scale)**														
**High anxiety score (≥50/100)**	23.3		23.8		24.3		24.4		23.7		22.5		25.7	
**High depression score (≥50/100)**	3.2		2.8		2.5		2.8		2.6		2.6		2.7	
														
**Duke Health Profile**														
**Physical score (0-100)**	75.4	0.5	75.1	18.9	75.6	18.5	75.3	18.6	75.5	18.7	76.1	18.6	74.6	18.7
**Mental score (0-100)**	64.4	0.6	64.8	23.4	63.9	23.3	64.0	23.6	64.7	23.1	65.1	23.1	63.5	23.6
**Social score (0-100)**	68.8	0.4	68.7	19.2	68.6	19.3	68.5	19.4	68.8	19.1	68.9	19.1	68.4	19.4

¶ Overall baseline characteristic parameters are estimated according to stratification and cluster design

* Data are mean when SD is displayed or percentages

** Standard Error of the Mean

¥ Standard Deviation

Nutritional guidelines the most likely to be improved by interventions are those for fruits and vegetables (13.5%), limiting nibbling (29.1%), sugary foods (34.1%), dairy products (42.0%) and physical activity (46.6%), as well as the number of nutritional guidelines followed (< 27% did not follow at least two-thirds of the nutritional guidelines). The mean nutritional knowledge score was only about half the total score and suggests an opportunity for improvement, especially for the educational strategy.

Higher ICCs (> 0.100) were observed for age, kind of course (general and technological or vocational), type of schooling, residence (rural or urban), knowledge score and waist circumference (see additional file 1: ICC 1, for overall and by strategy). Stratification increased the power greatly for all outcomes except gender, kind of course, residence and waist circumference (see additional file 2: ICC 2, for overall and by strategy).

Most of the students were half-time boarders (n = 3,766, 68.2%) and more often lived in urban areas (n = 2,663, 47.0%); 50.1% had parents who worked and 59.8% declared a high family income.

At baseline, 14.9% of adolescents were overweight (n = 792) and 4.6% were obese (n = 215). The mean BMI was 21.1 kg/m^2 ^(standard error of mean (SEM = 0.1), and was higher in girls than in boys (respectively 21.8 kg/m^2 ^(SEM = 0.1) vs 21.6 (SEM = 0.1)) but the sexes did not differ in overweight and obese proportion. Concerning family nutritional environment, 54.9% of students declared a low parent physical activity, and 39.1% reported that their parents were overweight. Some students were at high risk of psychological troubles: 8.8% of students were at high risk of eating disorders, 23.3% anxiety and 3.2% depression.

## Discussion

The need for randomised trials of complex interventions such as health promotion are high, but such trials are a relatively new phenomenon [2,3], and their role is still not self-evident in public health nutrition research. Clustering, multiple factorial and long-term duration are particularly suited for health promotion trials intended to provide high-quality evidence to support public health policy [30]. Such trials allow for implementing interventions in real conditions within appropriately diverse populations from heterogeneous settings and reporting on a broad range of health outcomes.

Cluster randomised trials are a common and necessary design for assessing community interventions, especially when they involve environmental actions and rely on interactions between subjects. This type of trial has methodological difficulties [31,32] and is still not well reported [33]. We paid attention to the building of clusters for representativeness at the regional level and a minimal clustering effect through stratification; to the sample size calculation, taking into account several ICC estimates for each outcome [31]; and finally to the reporting process according to the CONSORT statement extended for cluster randomized trials [28]. A limitation of clustered randomised trials is that the interventions cannot be blinded. This potential bias is minimized since we ensured randomisation by high school, that only school nurses are responsible for anthropometric measures, and the factorial plan created a combination of interventions.

The PRALIMAP trial incorporates a rare 2 × 2 × 2 factorial cluster randomised design. The design was selected to evaluate all 3 strategies and their potential synergy. Factorial designs have been used in individual randomised trials, but combined with clustering, fewer than 10 were 2 × 2 designs, and to our knowledge, only 1 was a 2 × 2 × 2 design [34].

The PRALIMAP trial duration is in line with the Sharma et al. recommendations to provide interventions longer than 6 months [35,36]. The PRALIMAP interventions spread out over 24 months allows for drawing conclusions that are sustainable in the long run.

High schools were included in 2 waves, of 8 and 16 schools each. We chose this format because we were unable to implement the interventions and the measurements at the same time in the 24 schools spread over a 23,547-km^2 ^area and including more than 2,000 professionals to be informed and trained. This design appears to be superior to an experimental pilot site, through the dynamics created between the 2 waves of high schools and the ability to respect the randomisation plan (balance between strategies according to stratification criteria). A wave effect will be looked for and, if needed, taken into account in the analysis.

We chose adolescents as the target for the PRALIMAP intervention. During adolescence, individuals develop responsibility for health-related behaviours and attitudes that affect their future [37,38]. Moreover, eating habits initiated during this time are long-lasting [39]. Eventually, a strategy based on fostering personal responsibility, cognitive self-regulation and competence could be effective in improving healthful eating and physical activity behaviours among middle school children [40]. We did not involve parents in the intervention because adolescents' increasing independence around food choice is described as an act of parental defiance and peer solidarity [41]. Adolescents resolve the conflict between their need for autonomy over their food choices and the needs of others in the family by making their own meals, eating out, eating what is served, and negotiating to have their own and other family members' food choices and needs met [42]. This behaviour is one of the reasons why we chose a school-based intervention as opposed to family or community interventions. Another reason was that educational skills of professional teachers should increase the effectiveness of lessons introduced into the curriculum. The school has been described as an ideal place to run prevention interventions considered an integral part of the educational mission in France [43], as well as internationally [5,44], and to avoid known financial barriers in prevention access.

In terms of national and regional academic programs, schools are free to choose the form in which they provide education for their students, and nutritional education programs such as that in the PRALIMAP trial are used in many French schools without the need to obtain parental consent. Moreover, schools modify their environment on their own. Parental consent is required not for the intervention per se but for the outcomes measurements. Although schools were randomly assigned without consent from adolescents and their parents, both groups received information and could decline to participate in completing questionnaires and measuring body size. Information, access to data and the right to withdraw participation is warranted by French law after approval by adequate committees.

Summerbell et al. reported that studies focusing on the combination of dietary and physical activity did not show a significant improvement in BMI but that some studies focusing on dietary or physical activity alone showed a small but positive impact on BMI status; however, nearly all studies found some improvement in diet or physical activity behaviour [3]. In contrast, Sharma et al. showed that interventions targeting both physical activity and dietary behaviour were successful in influencing adiposity indices [36]. The PRALIMAP trial aims to focus on both diet and physical activity (as part of an integrative nutritional approach) in each of the 3 strategies.

Nutritional education has been evaluated in adolescents in a few studies with varying design and effectiveness [2,35,45]. A systematic review of published and "grey" literature [35] reported a moderate effect in adolescents 13-18 years of age. However, most of these interventions were classroom-based activities with an adapted curriculum. The PRALIMAP trial involves lectures in a quantity corresponding to the median yearly number of hours devoted to this task in other countries [6] but also experiments with other kinds of education through autonomous collaborative works and nutritional parties. These activities may lead to better motivation in students, thanks to a more convivial, pleasant and positive approach to nutrition and to skills acquisition and empowerment.

The PRALIMAP screening strategy is a new concept of school-based screening combining school-based measurements of BMI associated with waist circumference to define overweight and obesity and school-based care. At the onset of the trial, this new approach aroused debates among high school professionals who considered that the high school should not be viewed as a place for health care and among health professionals who are not well trained in proactive strategies of health problems management, being more comfortable with subjects contacting them directly with a care demand. However, Kubik et al. [46] described schools as a setting for obesity prevention (primary and secondary) and particularly highlighted the school nurses' responsibilities as vital but underutilized in delivering school-based obesity prevention. Moreover, the American Institute of Medicine recommended in 2005 to measure BMI in school and to report the results to parents [5]. Some school-based screening programs, practice, and effectiveness have been evaluated, and guidance has been provided for implementing such an approach [6,12,47].

In the PRALIMAP trial, waist circumference is associated with BMI to determine overweight and obesity because this measurement is convenient, simple to measure, and correlated with BMI, an approximate index of total body fat, and can be used for longitudinal assessment in management [44,48]. The measurement allows for avoiding false positives among athletic students in specific "sports and study" programs.

The proposed care of the PRALIMAP relies on the therapeutic education concepts in a stepwise collective approach that split up the intervention into several stages delivered by a multidisciplinary team, as recommended by the US Preventive Services Task Force [49]. Behavioural interventions were reported as probably safe in children 4-18 years of age and can be effective [50]. Barton et al. [49] showed that low-intensity interventions may be feasible for primary care but did not demonstrate a significant consistent benefit with regard to BMI. However, evidence is still insufficient because of the limited number and sample size of available studies. In the PRALIMAP trial, the intensity of the intervention is low (10-14 hours), but weight outcomes are long term and the number of subjects is high.

The environmental strategy implies reconsideration of high school nutrition policy and functioning, which can be difficult for school staff. However, since 2007, such strategies must be undertaken in French schools with regard to the new recommendations for catering [51]. Moreover, high schools implementing the environmental strategy were specially funded by the Regional Council to help them improve dietary and physical activity school facilities and offerings. Only a few studies have evaluated school nutritional environment interventions, but none showed conclusive results in terms of adolescents' body size, and one found a positive long-term effect on only dietary behaviour [2,35,35,45,52]. In the PRALIMAP environmental strategy, a new tool was used to help catering staff improve meals by use of special software that allowed for observing food consumption every day and better adapting the offerings for students, especially for fruits and vegetables [53].

The environmental strategy features an annual nutritional party, but its objectives differ from those of the education strategy party. In the environmental strategy, the party aims to help students discover new foods and physical activities to let them diversify their energy intake and expenditure, whereas the educational strategy party is a pedagogic way to evaluate and improve knowledge.

Multicomponent interventions promoting a healthy diet have been evaluated in high school-aged adolescents in European Union countries. These interventions were of limited effectiveness for self-reported dietary behaviour, and only one included anthropometric measurements, and results were inconclusive [35]. Eating patterns are more likely to improve when changes in the school environment are integrated with classroom nutrition education [54]. "Making healthy choices easier" is a strong recommendation for combining both strategies and needs to be evidenced [55]. In fact, no study has assessed the effects of environment and education strategies and their interaction. Because of its factorial design, PRALIMAP allows for determining an interaction between strategies and thus could provide information on an expected greater effectiveness of the combination of consistent educational and environmental strategies. Moreover, it allows for investigating a higher order interaction with the screening strategy. The combination of the 3 strategies could gather all conditions that could contribute to improving the prevention of overweight and obesity.

The PRALIMAP is a pragmatic trial where interventions were implemented in the real context of high schools. Effectiveness [56] is evaluated through body composition measurements, nutritional behaviour and knowledge outcomes, as was recommended by some authors [35,45,57]. The PRALIMAP outcomes rely on anthropometric data collected by high school nurses and on self-reported measures such as knowledge and behaviours collected in the classroom setting. At baseline, we achieved a high participation rate for both types of measurements (85.7%). The availability of the Board of Education database allows for comparison of the sociodemographic differences between participants and non-participants and suggests a probable higher non-participation rate among overweight students. However, non-participation in the PRALIMAP measurements is similar across arms. The turnover with entry level and attrition at each grade is common in schools and is likely to reduce power and even introduce bias if these data differ by randomisation arm. The design offers the opportunity to analyse the data in a longitudinal cohort approach, as well as in a repeated cross sectional approach. It offers the opportunity to combine hard outcomes (body size) with declared and perceived outcomes [58] (self-administered questionnaires) to explore the hypothetical cause from knowledge to health. Questionnaires used were standardised internationally or specifically designed for PRALIMAP. The time interval between the second and last visit measurements was shorter in the vocational than general and technological high schools, but the stratification design allowed us to control for this difference.

A remarkable feature of the PRALIMAP is the extensive and comprehensive process evaluation. The trial was designed to investigate not only the outcomes relating to nutritional behaviours but also the processes involved in developing and implementing the intervention strategies, as well as the type of nutritional activities provided in the control schools for each strategy. This feature can help interpret observed relationships between the interventions and outcomes. A specific work is planned to provide an estimation of the dose of intervention, which will allow for more intensive analysis beyond a simple interpretation task by performing a per protocol statistical analysis including the dose of each strategy implemented in each high school.

In conclusion, the PRALIMAP trial aims to improve the prevention and management of overweight and obesity in adolescents by translating current evidence into public health practice. For almost 10 years, the French government has implemented a concerted nationwide strategy to reduce the prevalence of obesity at every age. Determining the most effective strategies to implement guidelines in schools is a major component of this program, which needs to be more successful in meeting the needs of subjects, particularly those from lower socioeconomic classes [59]. The results should inform how best to implement effective nutrition prevention programs in a school environment targeting adolescents at a time in their lives when they develop responsibilities and empowerment for health attitude behaviours. The initial results are expected in late 2010.

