	• Implementation of new features and activities to improve nutritional environment•	
	• Organization of a 1-day or half-a-day PRALIMAP party	

Three prevention strategies are used. By "Educational strategy", we mean developing personal skills to adopt healthy behaviours in the field of nutrition (diet and physical activity) according to current guidelines [7,8]. By "Screening strategy", we mean measuring, detecting overweight/obesity and eating disorders, and proposing if necessary an adapted care management. By "Environmental strategy", we mean developing favourable and supportive environments for healthy behaviours targeting the catering supply of the school and the school policy.

The 3 strategies are implemented in high schools according to standard operating procedures. All activities are performed over the first 2 high school years (corresponding to grades 10 and 11 in the US educational system) between January and June. These strategies target individual nutritional behaviour by acting directly on student skills (educational strategy and screening strategy) or by changing the school environment (environmental strategy).

The educational and environmental strategies are managed by trained health education professionals external to the high schools, called PRALIMAP monitors, specifically recruited for the trial. The monitors clarify objectives to be reached, propose and initiate activities and accompany and support high school professionals. The screening strategy is managed by public health professionals of Nancy-University, high school nurses and practitioners and an external nutrition health network.

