#### Screening strategy

Weight, height and waist circumference of students are measured twice in a single session by high school nurses in the nurse's office, and the Eating Attitudes Test 40 (EAT-40) and Hospital Anxiety and Depression (HAD) questionnaires are completed. All these data are part of the follow-up visit data collection.

The body weight of students wearing underwear is measured with an accuracy of 0.05 kg by use of a calibrated electronic scale (SECA^®^: model number 873 1321009). The body height of students not wearing shoes is measured by a stadiometer (SECA^®^: reference SECA 214 SEC 01) to the nearest 0.1 cm. The body mass index (BMI) is calculated as weight/height^2 ^from the mean of the above 2 measurements. We used the International Obesity Taskforce (IOTF) age- and sex-specific cut-off values for BMI for thinness grades 1, 2 and 3 [9], overweight and obesity [10], with dataset-specific centiles linked to adult cut-off values. Waist circumference is measured with use of a non-elastic flexible tape (SECA^®^: reference 200 SEC 01) at the level of the bellybutton to the nearest 0.1 cm with the subject in a standing position. We use the McCarthy [11] age- and sex-specific cut-off values to define high waist circumference using dataset-specific centiles linked to adult cut-off values. A positive screening is defined by an overweight or obesity according to BMI and high waist circumference.

An EAT-40 score ≥ 30 (on a 0-120 scale) is used as a cut-off value to identify students suspected of having eating disorders. HAD scores ≥ 11 (on a 0-21 scale) is used as a cut-off value to identify students suspected of having anxiety and/or depression.

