Nurses notify students with positive screening orally and in writing, explain the consequences of overweight and the importance of adapted care management, and give them letters containing the screening results, including EAT-40 and HAD scores, one for their parents and one for their general practitioner. As recommended by Nihiser et al. [12], the letter to parents typically includes the child's BMI-for-age percentile, an explanation of the results and recommendations for care management. The adapted care management consists of 7 group educational sessions, offered for 1.5 hours by physicians, dieticians, sport educators and psychologists. These sessions are implemented outside of the high school by an external healthcare network specialized in nutrition or inside the high school by a mobile team if a network is not available in the surrounding territory of the high school. These sessions are funded by the regional health insurance system.

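### Measurement by school nurses separates assessor from deliverer for the educational and environmental strategies but not for the screening strategy, which school nurses help to deliver

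*Protocol article*

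**What the plan says.** The Discussion of the protocol article is open about the lack of masking: "A limitation of clustered randomised trials is that the interventions cannot be blinded". It then gives three reasons why the resulting bias is small. Two are in this sentence: "This potential bias is minimized since we ensured randomisation by high school, that only school nurses are responsible for anthropometric measures". The third is that "the factorial plan created a combination of interventions".

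Who delivers what is set out under Study Interventions. For two strategies: "The educational and environmental strategies are managed by trained health education professionals external to the high schools, called PRALIMAP monitors". For the third: "The screening strategy is managed by public health professionals of Nancy-University, high school nurses and practitioners and an external nutrition health network".

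The Screening strategy section adds the nurses' tasks. They take the readings: "Weight, height and waist circumference of students are measured twice in a single session by high school nurses in the nurse's office". They also act on a positive result: "Nurses notify students with positive screening orally and in writing, explain the consequences of overweight and the importance of adapted care management". They hand over the result letters for parents and general practitioner as well. Table 2 repeats the measurement and notification in grade 11 and names a medical professional alongside the nurses for notification. On the use of the readings, the same section says: "All these data are part of the follow-up visit data collection".

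Under Outcomes and process data, the main endpoint is the change in overweight and obesity prevalence over the two intervention years, which rests on these measurements. No masked or independent assessor is described.

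**The concern.** In an open trial, a statement about who takes the outcome reading is reassuring only if that person has no part in the intervention. The article makes the statement for all three strategies at once, but its own account of roles supports it for two. In screening schools the professional group that takes the T1 and T2 readings has also told students that they screened positive and encouraged them to accept care. In the other schools the documents give nurses a measuring role only. The difference in role follows the screening factor exactly.

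The endpoint is a dichotomy at a BMI cut-off, so a modest systematic difference in readings between screening and non-screening schools would move prevalence. If a favourable screening result appeared, the article as written would defend it with a protection that this comparison does not have.

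**Working it through.** **Roles side by side**

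| Strategy | Managed by | Body size measured by | Assessor separate from deliverer? |
|---|---|---|---|
| Educational | external monitors (teachers give the lectures) | school nurses | yes |
| Environmental | external monitors | school nurses | yes |
| Screening | university public health staff, school nurses and practitioners, outside nutrition network | school nurses | no |

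Screening is assigned in groups A, C, E and G. With 3 schools per group that is 4 × 3 = 12 of 24 schools.

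**Do the other two reasons help?** Randomisation by school balances schools at entry but does not act on how a reading is taken at T1 or T2. The factorial plan balances the other strategies across the screening comparison, but the nurses' extra role is part of the screening factor itself. Neither restores the missing separation.

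**Which visits?** Notification follows from the T0 reading, so T0 precedes it. The concern is T1 and T2. Because the endpoint is change over time, a misreading habit already present at T0 and constant afterwards would largely cancel. What matters is a difference arising after T0.

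**The plan's own figure.** Sample size section: 5,475 students, cluster size 228, ICC 0.005.
- Design effect = 1 + (228 − 1) × 0.005 = 2.135.
- Effective number per level of one factor = 5,475 / 2 / 2.135 = 1,282.
- Detectable decrease at two-sided 5% (sidedness assumed) and 80% power: 3.7 points from 15%, 4.1 from 18%, 4.2 from 19.5%. The control prevalence is not stated in that section. The stated figure of approximately 4% is reproduced.

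**Scale of a uniform misreading (illustration).** Inputs: mean BMI 21.6 and SD 3.5, within the by-strategy range of Table 5; prevalence 14.9% + 4.6% = 19.5%; mean height 168 cm (assumed); log-normal BMI (assumed); one cut-off for all students (a simplification).
- σ = √ln(1 + (3.5/21.6)²) = 0.161; μ = ln 21.6 − σ²/2 = 3.060; cut-off = exp(3.060 + 0.161 × 0.860) = 24.5.
- Height read 0.5 cm too tall: BMI is multiplied by (168/168.5)² = 0.9941; prevalence becomes 18.5%, a fall of 1.0 point (1.1 under a normal distribution).
- Height read 1 cm too tall: factor (168/169)² = 0.9882; prevalence becomes 17.5%, a fall of 2.0 points (2.2 under a normal distribution).

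**Misreading of notified students only.** A positive screen needs overweight or obesity together with a high waist. Assume a BMI–waist correlation of 0.7 to 0.9, a high-waist prevalence of 11.7 to 13.4% (Table 5, Canada classification; the prevalence under the screening definition is not given) and no BMI change between visits. The fall is then about 0.2 points for 0.5 cm and 0.4 to 0.5 points for 1 cm.

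**Effect on error rate.** With no true effect, SE = √(2 × 0.195 × 0.805 / 1,282) = 0.0156. A spurious shift of 1 point raises the two-sided 5% false-positive rate to about 10%; 2 points raises it to about 25%.

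**The case against.** The strongest reply is that the documents show no bias and describe real protection. Weight is taken on a calibrated electronic scale, height on a stadiometer to 0.1 cm, BMI comes from the mean of two readings, and trained nurses measure in all schools. An outside team runs the seven care sessions. The article says minimised, not eliminated, and admits first that there is no blinding. All of this stands and limits the risk. It does not make nurse measurement a safeguard for screening: both readings are taken in one session by staff who are not masked.

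The reply is also right about several stronger readings.
- A reader might infer that the arrangement produces bias in favour of screening. The documents support a risk only, and not its direction: T1 is itself a screening visit, where reading students low would work against the nurse's detection task.
- A reader might infer that one nurse classifies the student, knows the earlier status and takes every later reading. The article does not say who calculates BMI or applies the cut-offs, nor that one nurse serves all visits.
- A reader might take 1 to 2 points as the expected bias. That needs every student in all 12 screening schools to be misread by 0.5 to 1 cm, five to ten times the stadiometer's resolution. Confined to notified students, the shift is 0.5 points or less under the assumptions above.

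**Conclusion.** The point holds as a limit on one statement in the Discussion. Nurse measurement separates assessor from deliverer for the educational and environmental strategies. It does not for screening, where outcome readings are taken by unblinded co-deliverers, and neither randomisation by school nor the factorial plan changes that. The consequence is a risk of differential assessor bias in the screening comparison at T1 and T2.

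The documents give no size for this bias. The range above, from about 0.2 points (0.5 cm, notified students only) to about 2 points (1 cm, all students), is an illustration resting on an assumed height, BMI distribution and BMI–waist correlation. Its upper end is about half the planned difference and should be read as an extreme case. The design can stand; the text and the interpretation of the screening result need to change.

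**What to change.** 1. In the Discussion, confine the statement about nurse measurement to the educational and environmental strategies.
2. State that body-size outcomes for the screening comparison are assessed by unblinded co-deliverers, and interpret a favourable screening result on prevalence with that limitation.
3. Where the raw readings were kept (the article mentions only their mean), report by screening arm, at T1 and T2, end-digit heaping and the density of BMI just below and just above the cut-off. This checks for selective misreading near the cut-off; it cannot exclude a uniform shift. Differences between the paired readings and mean BMI in all students are not substitutes, since a uniform shift is common to both readings of a session and carries into the mean.
4. For any visits still to come, record raw readings without access to earlier values or BMI category. This may have little to act on: wave 2 entered grade 10 in 2007 and reached grade 12 in 2009, and the article appeared in December 2010.

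The cost is a less favourable statement about blinding and a small extra analysis of existing data.
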